# Evaluation of the efficacy of transcranial direct current stimulation in the treatment of cognitive symptomatology in the early stages of psychosis: study protocol for a double-blind randomized controlled trial

**DOI:** 10.1186/s13063-019-3288-5

**Published:** 2019-04-05

**Keywords:** Early stages of psychosis, Schizophrenia, Neuromodulation, Transcranial direct current stimulation, Neuropsychology, Cognitive symptomatology, Double-blind randomized controlled trial

## Abstract

**Background:**

Cognitive deficits are core symptoms of schizophrenia that occur from the early stages of the disorder. There is reliable evidence that cognitive deficits are associated with outcomes in schizophrenia; thus, early treatment could be particularly important. Studies with different neuromodulation techniques involving subjects with schizophrenia suggest that application of transcranial direct current stimulation (tDCS) with inhibitory stimulation over the left temporo-parietal cortex and excitatory stimulation over the left dorsolateral prefrontal cortex could ameliorate positive, negative, and cognitive symptoms.

The aim of the present study protocol is to evaluate the efficacy of tDCS in the treatment of cognitive symptomatology in the early stages of psychosis.

**Methods/design:**

Seventy patients in the early stages of psychosis will be randomly allocated to receive 20 min of active 2-mA tDCS or sham stimulation once a day for 10 consecutive weekdays. The anode will be placed over the left dorsolateral prefrontal cortex and the cathode over the left temporo-parietal cortex. Neuropsychological and psychiatric assessments will be performed at baseline and at 1 and 3 months following the end of the intervention (sustained effect).

**Discussion:**

The development and utilization of potentially effective neuroenhancement tools such as the non-invasive brain stimulation technique tDCS for the treatment and rehabilitation of cognitive impairment in the early stages of schizophrenia may contribute to improving outcomes of the disorder and eventually provide a further understanding of the nature of the complex and dynamic neural processes underlying those abnormalities.

**Trial registration:**

ClinicalTrials.gov, NCT03071484. Registered on 7 March 2017.

**Electronic supplementary material:**

The online version of this article (10.1186/s13063-019-3288-5) contains supplementary material, which is available to authorized users.

## Background

### Scientific background and explanation of rationale

Schizophrenia, the most common condition among psychotic disorders, is a serious mental disorder that has a great impact on public health, accounting for about 10% of disability among persons aged 15–44 [28] and reduced life expectancy by more than 15 years [3]. The lifetime prevalence of schizophrenia is estimated at between 0.5 and 1% in the general population, with a slightly higher rate for males [4].

Different sources of evidence support the hypothesis that the etiology of psychoses is multifactorial and includes genetic, environmental, cognitive, and psychosocial factors [8]. Usually, the clinical manifestations occur between late adolescence and early adulthood. In recent decades, these manifestations have been considered premorbid stages in the description of the clinical history of psychosis, as different studies have suggested that early interventions can positively impact the prognosis of the disease [4].

Over the past 20 years there has been a major shift in the paradigm of how we understand psychoses. Consistent evidence addresses these diseases with complex genetic and multifactorial etiology as being associated with brain changes that occur throughout neurodevelopment, and not just as processes that settle and progress with the onset of symptoms (neurodegeneration) [1]. Psychosis mechanisms begin to be understood as due to abnormal changes in brain circuits that culminate in clinical manifestations of the disease which, in turn, establish progress and neurodegenerative processes related to their course. From this perspective, a model of clinical stages was developed which provides for a gradual transition from normal (stage 0) to the disease state (stage 2), including a prodromal stage (stage 1) in which symptoms are non-specific, heterogeneous, and unstable in time, coalescing and progressively differentiating to culminate in the typical feature of the disease [19]. This model represents a break in the current dichotomy between normality and disease, enabling the development of effective strategies for primary, secondary, and tertiary stages. The model has motivated a growing interest in finding specific biomarkers of steps leading to the manifestation of psychosis, to implement early intervention with the potential to improve prognosis by reducing the mortality and morbidity associated with the disease.

Different studies have shown that cognitive impairments are present before the onset of schizophrenia, remain after remission of psychosis symptoms, and can often be found in first-degree unaffected relatives, suggesting that neurocognitive alterations are a feature of psychosis which influence social and interpersonal skills, leading to an impairment of social cognition. This explains much of the variance-related functional impairment [12–15].

Those findings have encouraged a proliferation of research on neurocognitive enhancement aiming at the development of potentially effective treatment and rehabilitation of cognitive symptoms in patients with schizophrenia. In this scenario, characterized by a growing interest in developing novel neuroenhancement techniques, implementing non-invasive brain stimulation techniques aroused a new age in systems neuroscience research in which research examining the modulation of cognition using transcranial direct current stimulation (tDCS) is one of the most rapidly advancing fields in cognitive neuroscience. Recent studies have demonstrated significant, often strong, effects of tDCS on cognitive processes [10].

The tDCS is a non-invasive neuromodulatory technique that delivers low-intensity, direct current to cortical areas facilitating or inhibiting spontaneous neuronal activity and its plasticity [7, 27]. Although there are many brain stimulation techniques, tDCS is a low-cost and portable method that is well tolerated by participants, especially when compared with other techniques. In addition, there is no report of serious risks associated with treatment with tDCS in the literature. Possible adverse events related to the method usually include mild and transient conditions which do not require specific intervention, such as local redness and discomfort, mild headache, and, in rare cases, minor burns at the electrode placement site. However, all these events can be easily avoided by monitoring during the procedure [10, 24].

In patients with schizophrenia, tDCS has been demonstrated to be potentially useful for the treatment of positive symptoms [6] as well as cognitive symptoms [26]. Recent findings suggest that repetitive stimulation over specific time intervals may be a promising option to increase the efficacy of tDCS [24]. Additionally, Palm et al. [26] reported an improvement of 25% of the negative symptomatology in a case report study, and these results reflected a reduction of 12% in the total score of the Positive and Negative Syndrome Scale (PANSS).

Despite the established efficacy in the treatment of psychotic (positive) symptomatology, antipsychotics have been largely ineffective in treating cognitive deficits and negative symptoms associated with psychoses [21]. Neuropsychological deficits are present since the onset of the disease [2] and are considered nuclear symptoms in psychosis, exhibiting a marked impact on overall functioning [5]. Robust evidence suggests that the longer the time to start treatment, the worse the clinical evolution of the patient, reinforcing the importance of early diagnosis and treatment [11].

The efficacy of tDCS in improving cognitive deficits in both neurological and psychiatric conditions has been amply demonstrated in the literature. As cortical stimulation has a positive effect on short-term cognition, studies emphasized that stimulation may bring benefits to the potential of rehabilitation in patients with cognitive impairment as well [23]. However, as far as we know, there is no study examining the effects of tDCS on cognition in the early stages of psychosis.

Given the importance of reentering individuals with schizophrenia to the community, the Measurement and Treatment Research to Improve Cognition in Schizophrenia (MATRICS) initiative of the US National Institute of Mental Health (NIMH) set the development of a Consensus Cognitive Battery (MCCB) for measuring cognition in schizophrenia, aiming to guide the design of clinical trials for cognition-enhancing agents and encouraging new research [16–18], which will be used in this present study protocol.

### Objectives

The aim of the present study protocol is to evaluate the efficacy of tDCS in the treatment of cognitive symptomatology in the early stages of psychosis. We hypothesized that the patients randomly allocated to the experimental group will demonstrate a significant better performance on cognitive processes in comparison to those in the matched control group.

## Methods/design

### Trial design

The design of the present study protocol is a double-blind, placebo-controlled randomized clinical trial.

After being randomly allocated, the experimental group will receive 20 min of active 2-mA tDCS once a day for 10 consecutive weekdays. The control group will receive a sham stimulation (placebo); the chosen parameters are that, after 40 s of real stimulation (2 mA), only a small current pulse occurs every 550 ms (110 mA over 15 ms) through the remainder of the 20-min period.

Neuropsychological and psychiatric assessments will be performed at the time of consent (baseline) and at 1 and 3 months following the end of the intervention (maintenance effect). The primary outcome will be cognitive function; the secondary outcomes will be the positive and negative symptoms. Outcome assessments will be performed by trial research staff. Primary and secondary outcome assessors (neuropsychologists and psychiatrists) and patients will be blinded to randomized allocation after assignment to the interventions.

The present study protocol was written in compliance with the Standard Protocol Items: Recommendations for Interventional Trials (SPIRIT) 2013 [9]. A completed SPIRIT checklist is available as a supplement (Additional file 1), and the schedule of this study is presented in Fig. 1. The study flowchart is shown in Fig. 2.

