### Intervention

We have chosen tDCS, a non-invasive brain stimulation technique that involves the passage of a small current through the scalp and skull to modulate brain activity [10]. The electric current will be delivered by an electric stimulator (Striat, Ibramed Indústria Brasileira de Equipamentos Médicos Ltd., Sao Paulo, Brazil). In this study protocol, saline solution will be applied to sponge electrodes, which will be placed according to the international 10–20 electrode placement system. The anode will be placed with the middle of the electrode over a point midway between F3 and FP1 (left prefrontal cortex: dorsolateral prefrontal cortex, assumed to correspond to a region including Brodmann areas [BA] 8, 9, 10, and 46, depending on the subject), and the cathode will be placed over a point midway between T3 and P3 (left temporo-parietal junction, assumed to correspond to a region including BA 22, 39, 40, 41, and 42). In accordance with recent studies of tDCS in schizophrenia, the stimulation level will be set at 2 mA for 20 min. The stimulation sessions will be conducted once a day for 10 consecutive weekdays. The chosen sham/placebo stimulation parameters for the control group will be the following: after 40 s of real stimulation (2 mA), only a small current pulse will occur every 550 ms (110 mA over 15 ms) through the remainder of the 20-min period [6, 29].

No changes will be required in the ongoing treatments with other professionals, and the subject may request to discontinue at any time. Although there is no description of serious risks associated with treatment with transcranial direct current stimulation in the literature, possible adverse events related to the method, including mild and transient conditions, which do not require specific intervention, may occur*.* In case of any persistent adverse event, participants will be treated by staff of PROESQ, Department of Psychiatry, UNIFESP, Sao Paulo, Brazil.

To avoid any harm, subjects will be monitored by a trained staff from the Center for Neuromodulation Studies, Universidade Federal de São Paulo, during the procedure. Subjects will be instructed to inform of any discomfort, so the power can be turned off immediately.

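### As written, the sham pulse of 110 mA is 55 times the active current and averages 3.0 mA, so controls would receive more charge than treated patients

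*Protocol article*

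**What the plan says.** The Protocol article specifies the two arms under Trial design and again under Intervention.

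- **Active arm.** Trial design: "the experimental group will receive 20 min of active 2-mA tDCS once a day for 10 consecutive weekdays". Intervention gives the same setting: "the stimulation level will be set at 2 mA for 20 min".
- **Sham arm.** Under Trial design, a control session opens with a 40 s lead-in at the active level of 2 mA. For what follows, that section says: "only a small current pulse occurs every 550 ms (110 mA over 15 ms"). The pulsing lasts until the session ends. Intervention repeats the amplitude, width and interval: "only a small current pulse will occur every 550 ms (110 mA over 15 ms) through the remainder of the 20-min period". It cites two sources for these parameters.

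No other section gives a different amplitude or unit for the sham pulse. The Background describes tDCS as a low-intensity technique, and Trial design calls the control a placebo.

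**The concern.** The sham should be close to electrically inert once its 40 s lead-in is over. The text calls the following pulse small but prints an amplitude far above the therapeutic current. Because the pulse repeats roughly twice a second for over 19 minutes, the short pulse width does not necessarily make the exposure negligible, so the average has to be worked out.

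Two consequences are possible, depending on what the devices do:

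- **The devices follow the printed value.** Control patients receive a larger electrical exposure than treated patients. That is a safety problem, and it removes the placebo contrast on which the efficacy hypothesis in Objectives rests.
- **The devices do something else.** The published control condition is not the one delivered. Nobody can replicate the trial or judge the adequacy of its sham from this text.

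**Working it through.** The article derives no mean current or charge, so there is no figure of its own to reproduce. The check sets its stated settings against each other.

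**Inputs (Trial design; amplitudes and timings repeated under Intervention)**

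- Active: 2 mA for 20 min = 1200 s.
- Sham lead-in: 2 mA for 40 s.
- Sham pulse: 110 mA, 15 ms wide, every 550 ms.
- Sham pulse phase: 1200 − 40 = 1160 s.

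**Formulas**

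- Mean pulse current = amplitude × width / period.
- Charge (mC) = current (mA) × time (s).

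**Plain reading: constant 110 mA during each pulse, 550 ms as the full period**

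1. Amplitude ratio: 110 / 2 = 55.
2. Duty cycle: 15 / 550 = 2.73%.
3. Mean pulse current: 110 × 15 / 550 = 3.0 mA, against 2 mA active.
4. Active charge per session: 2 × 1200 = 2400 mC.
5. Sham charge per session: 2 × 40 + 3.0 × 1160 = 80 + 3480 = 3560 mC.
6. Ratio: 3560 / 2400 = 1.48.

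**How far this depends on the reading**

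| Reading of the pulse | Mean pulse current (mA) | Sham charge (mC) | Sham / active |
|---|---|---|---|
| 110 mA, constant, 550 ms period | 3.0 | 3560 | 1.48 |
| 110 mA, constant, 550 ms gap (565 ms cycle) | 2.92 | 3468 | 1.44 |
| 110 mA as the peak of a triangular pulse, 550 ms period | 1.5 | 1820 | 0.76 |
| 110 microamperes, constant, 550 ms period (assumed unit) | 0.003 | 83.5 | 0.035 |

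**Break-even amplitude.** For a constant pulse and a 550 ms period, sham charge equals active charge at (2400 − 80) / 1160 × 550 / 15 = 73.3 mA. The printed 110 mA is well above this.

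In the microampere row, 80 of the 83.5 mC come from the lead-in and only 0.003 × 1160 = 3.48 mC from the pulses. That does fit a pulse called small.

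**The case against.** The strongest reply is that this is plainly a misprint. The article calls the pulse small, the arm a placebo and the technique low-intensity; 110 mA fits none of these, and a slip of unit prefix makes the description coherent. This is probably right, but it does not remove the finding. The microampere unit is an inference that the article never states, and the error sits in the only definition of the comparator, in both places where it is given.

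Other points, and what stands of them:

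- **Waveform.** The text does not say that the pulse is rectangular. With a triangular pulse peaking at 110 mA, sham charge is 76% of active, so the statement that controls receive more charge depends on the constant-amplitude reading. That caveat stands. The 55-fold amplitude conflict does not depend on pulse shape, and a sham carrying 76% of the active charge would not be inert either.
- **Delivery is unproven.** Nothing in the article says that operators enter the pulse amplitude by hand or that the stimulator can produce 110 mA. Trained staff monitor sessions and can switch off the current. This makes undetected delivery at that level less plausible, and the safety consequence is rightly stated as conditional. But the article gives no output limits for the device, so the possibility cannot be dismissed from the text.
- **Replication.** The stimulator is named and sources are cited, so a replicator has somewhere to look. Whether those sources settle the value cannot be judged from the article.
- **Loss of a micro sign in text conversion.** This is possible but unlikely: Greek letters survive in the sample size section, and both occurrences read the same.

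**Conclusion.** The concern holds. The sham amplitude is wrong as written. It is 55 times the active current under any waveform. On the plain reading it averages 3.0 mA and gives 3560 mC per session against 2400 mC active, a ratio of 1.48 (1.44 if 550 ms is the gap between pulses). The charge comparison assumes a constant amplitude over the 15 ms.

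The defect is an internal contradiction in an operating parameter, most likely of unit. It does not show that any control patient was over-exposed. It must still be fixed, because it affects the definition of the control condition in a trial that Trial status describes as ongoing, and the correct value cannot be recovered from the document.

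**What to change.** 1. Measure the stimulator's actual output in sham mode on the bench before the next session.
2. Reconcile the amplitude and unit with the stimulator's technical specification and with the sources cited for the sham under Intervention.
3. Correct Trial design and Intervention together. Stating the waveform, and whether 550 ms is the period or the gap, would remove the remaining ambiguity.
4. Confirm from device settings or session records that no session was run at the printed value. If any was, treat it as a safety matter and reconsider how those control patients contribute to the comparison.

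The cost is a correction notice, a bench check and a look at the records. Correcting the text needs no change to the design, sample size or analysis.

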**Fig. 1 Fig1:**
[figure not shown]
Schedule of the trial interventions and assessments

**Fig. 2 Fig2:**
[figure not shown]
Flowchart of the trial

### Participants

Recruitment to the trial will be at the Schizophrenia Program (PROESQ), Department of Psychiatry, Federal University of São Paulo (UNIFESP), Sao Paulo, Brazil.

The inclusion criteria include the following: (1) subjects of both genders, diagnosed with schizophrenia in early stage psychosis (first 5 years of illness), confirmed through the Structured Clinical Interview for the American Psychiatric Association Diagnostic and Statistical Manual of Mental Disorders, 5th edition (SCID-5); (2) aged 18–60 years; (3) minimum of 4 years of education; (4) intelligence quotient (IQ) from low average to higher scores (IQ > 70); and (5) the subjects should be receiving stable doses of antipsychotics for at least 4 weeks (antipsychotic dose stability criterion).

The exclusion criteria include (1) presence of a history of cranioencephalic trauma with loss of consciousness with a time greater than 5 min; (2) history of central nervous system diseases that affect the brain; (3) unstable clinical conditions; (4) use of drugs that affect cognitive performance such as benzodiazepines and anticholinergic agents; (5) current diagnosis of substance abuse; (6) history of substance dependence in the last 6 months, except nicotine addiction; (7) current diagnosis of another Axis I condition, confirmed through SCID-5.

Regular meetings with staff will be performed in order to clarify the study design and population. The research team will regularly contact the participants by phone to improve retention.

### Intervention

We have chosen tDCS, a non-invasive brain stimulation technique that involves the passage of a small current through the scalp and skull to modulate brain activity [10]. The electric current will be delivered by an electric stimulator (Striat, Ibramed Indústria Brasileira de Equipamentos Médicos Ltd., Sao Paulo, Brazil). In this study protocol, saline solution will be applied to sponge electrodes, which will be placed according to the international 10–20 electrode placement system. The anode will be placed with the middle of the electrode over a point midway between F3 and FP1 (left prefrontal cortex: dorsolateral prefrontal cortex, assumed to correspond to a region including Brodmann areas [BA] 8, 9, 10, and 46, depending on the subject), and the cathode will be placed over a point midway between T3 and P3 (left temporo-parietal junction, assumed to correspond to a region including BA 22, 39, 40, 41, and 42). In accordance with recent studies of tDCS in schizophrenia, the stimulation level will be set at 2 mA for 20 min. The stimulation sessions will be conducted once a day for 10 consecutive weekdays. The chosen sham/placebo stimulation parameters for the control group will be the following: after 40 s of real stimulation (2 mA), only a small current pulse will occur every 550 ms (110 mA over 15 ms) through the remainder of the 20-min period [6, 29].

No changes will be required in the ongoing treatments with other professionals, and the subject may request to discontinue at any time. Although there is no description of serious risks associated with treatment with transcranial direct current stimulation in the literature, possible adverse events related to the method, including mild and transient conditions, which do not require specific intervention, may occur*.* In case of any persistent adverse event, participants will be treated by staff of PROESQ, Department of Psychiatry, UNIFESP, Sao Paulo, Brazil.

To avoid any harm, subjects will be monitored by a trained staff from the Center for Neuromodulation Studies, Universidade Federal de São Paulo, during the procedure. Subjects will be instructed to inform of any discomfort, so the power can be turned off immediately.

### Outcome measures

At all assessment interviews, including neuropsychological and psychiatric, at the time of consent (baseline), and at 1 and 3 months following the end of the intervention (maintenance effect), IQ estimate and functioning will be tested in addition to the collection of standard demographic information. For this purpose, the Wechsler Adult Intelligence Scale Third Edition (WAIS-III) and the Personal and Social Performance Scale (PSP) will be used.

The WAIS-III is a standardized instrument for measuring the intellectual functioning and overall capacity of an individual [30, 31]. In order to measure the estimated IQ of the subjects under study, two WAIS-III subtests were selected, one to measure verbal and crystallized intelligence (Vocabulary) and another to measure non-verbal and fluid intelligence (Matrix Reasoning).

The Vocabulary subtest of the WAIS-III is a measure of verbal knowledge and crystallized intelligence. The version that will be used consists of 33 items. The task is to define a certain term, for example, “what is a BED?”. The examinee must include in his answer essential characteristics that define the specified term. Simple correct answers, usually involving a concrete aspect of the term, are scored as score 1, and correct complex answers receive score 2. Incorrect answers are scored as 0 [31].

The Matrix Reasoning subtest of the WAIS-III is a measure of abstract reasoning and execution and fluid intelligence. The subtest has 26 items, plus the three that serve as examples. It consists of four types of items: continuous and discrete patterns, classification, analog reasoning, and serial reasoning. The task requested of the examinee is to complete a series of incomplete patterns, pointing out or saying the correct answer number among the five alternatives presented [31].

The PSP is a validated clinician-administered scale that measures personal and social functioning in the domains of (1) socially useful activities, including work and study; (2) personal and social relationships; (3) self-care; and (4) disturbing and aggressive behaviors [22].

